## Abstract

**Introduction:**

Meta-analyses show postive effects of telemedicine in heart failure (HF) management on hospitalisation, mortality and costs. However, these effects are heterogeneous due to variation in the included HF population, the telemedicine components and the quality of the comparator usual care. Still, telemedicine is gaining acceptance in HF management. The current nationwide study aims to identify (1) in which subgroup(s) of patients with HF telemedicine is (cost-)effective and (2) which components of telemedicine are most (cost-)effective.

**Methods and analysis:**

The RELEASE-HF (‘REsponsible roLl-out of E-heAlth through Systematic Evaluation – Heart Failure’) study is a multicentre, observational, registry-based cohort study that plans to enrol 6480 patients with HF using data from the HF registry facilitated by the Netherlands Heart Registration. Collected data include patient characteristics, treatment information and clinical outcomes, and are measured at HF diagnosis and at 6 and 12 months afterwards. The components of telemedicine are described at the hospital level based on closed-ended interviews with clinicians and at the patient level based on additional data extracted from electronic health records and telemedicine-generated data. The costs of telemedicine are calculated using registration data and interviews with clinicians and finance department staff. To overcome missing data, additional national databases will be linked to the HF registry if feasible. Heterogeneity of the effects of offering telemedicine compared with not offering on days alive without unplanned hospitalisations in 1 year is assessed across predefined patient characteristics using exploratory stratified analyses. The effects of telemedicine components are assessed by fitting separate models for component contrasts.

**Ethics and dissemination:**

The study has been approved by the Medical Ethics Committee 2021 of the University Medical Center Utrecht (the Netherlands). Results will be published in peer-reviewed journals and presented at (inter)national conferences. Effective telemedicine scenarios will be proposed among hospitals throughout the country and abroad, if applicable and feasible.

**Trial registration number:**

NCT05654961.

STRENGTHS AND LIMITATIONS OF THIS STUDYA strength of this study is the use of nationwide routine clinical care data linked to national registry databases to capture current data on telemedicine use, the characteristics of patients with heart failure, treatments and clinically relevant outcomes with a 1-year follow-up.Another strength is that data from the heart failure registry in the Netherlands and a separate data collection on telemedicine features using additional questionnaires allow consideration of heterogeneous treatment effects across the heart failure population and telemedicine components.A limitation is that most data on telemedicine characteristics will be collected at the hospital level, rather than at the individual patient level.Another limitation is that the cost-effectivity analyses are specific to the Dutch healthcare system, which may hamper generalisability of findings to other settings or countries.A final limitation is that selection bias can occur when healthcare providers do not include all patients in the outpatient clinic in the heart failure registry because the registry is not incorporated in care pathways in electronic health record systems.

## Introduction

Heart failure (HF) poses a major socioeconomic and patient burden, and healthcare systems are seeking innovative health models to support care. Optimised guideline-directed medical therapy, self-care (ie, healthy diet, medication adherence, exercise) and adequate monitoring of vital signs and symptoms may all help reduce HF-related morbidity.^1–3^ Health models therefore use telemedicine as a tool to support patients in optimising HF management, self-care support and symptom monitoring to improve care and prevent (re)hospitalisation.^2–4^ ‘Telemedicine’ is a heterogeneous intervention that includes a wide range of digital technologies (smartphones, mobile wireless devices/sensors, video connections, implantable devices, etc) exchanging digital health information between patients and clinicians to support and optimise the care process remotely.^5 6^

Many meta-analyses have evaluated the (cost-)effectiveness of telemedicine in patients with HF.^7–19^ Overall, these meta-analyses point towards a positive effect of telemedicine on hospital admission, length of hospital stay, mortality and costs.^2 7–19^ However, the effects are heterogeneous across subgroups^20–24^ and vary with telemedicine components, such as type of monitored functions, number of alerts and risk of alert fatigue, contact with healthcare professional, type of device, and different quality of usual care.^7 14 15 19 25^ This can lead to problems in comparability of studies. Understanding of the cost-effectiveness of telemedicine is fragmented because studies do not evaluate the same costs, with the focus shifting between the purchase costs of telemedicine, personnel costs and variation in the costs of telemedicine components.^4 12 16^

As a result, HF guidelines lack specific recommendations on *how*, *when* and in *whom* telemedicine should be provided. Despite the lack of solid evidence and advice, payers (eg, procurement officers, insurance companies) and patient organisations are advocating to accelerate the implementation of telemedicine for patients with HF in outpatient clinics.^26^ Consequently, telemedicine is implemented in different formats with varying objectives, intervention components and implementation strategies. To reveal the real potential of telemedicine for patients with HF and its implementation in everyday practice, clarity on *how*, *when* and in *whom* and which telemedicine components are (cost-)effective is essential.

Here, we present the protocol for the RELEASE-HF (‘REsponsible roLl-out of E-heAlth through Systematic Evaluation – Heart Failure’) study. In this study, we focus on both patient-related uncertainties in telemedicine use and telemedicine intervention-related uncertainties from a clinical as well as an economic perspective. Our specific study objectives are to examine (1) which patient characteristics are related to an increase in the number of days spent alive without unplanned hospitalisations within 1 year when telemedicine is part of HF care compared with regular HF care; (2) which components of telemedicine as part of HF care lead to an increased number of days alive without unplanned hospitalisations within 1 year; (3) which characteristics of patients with HF are related to cost-effectiveness when telemedicine is part of HF care compared with regular HF care; and (4) which components of telemedicine as part of HF care are cost-effective.

## Methods and analysis

### Study design

RELEASE-HF is a nationwide, observational, registry-based cohort study across multiple hospitals in the Netherlands.^27^ The study collects routine data longitudinally. We record the health status of and cardiac interventions in patients with HF and simultaneously observe the natural (de)implementation of telemedicine. RELEASE-HF is linked to the Heart4Data consortium which started in 2022 to create a national and sustainable infrastructure for cardiovascular registry-based research in the Netherlands.^28^ This infrastructure will develop a framework for the governance, ethical, legal, financial, information technology and methodological factors necessary for registry-based research.

### Progress and time plan

RELEASE-HF started in June 2021 and will last 4 years (figure 1). This study includes a collaboration with at least 29 hospitals that signed a letter of commitment. Additional hospitals may enter the study later if they can complete a 12-month follow-up per included patient through the HF registry.

**Figure 1 F1:**
[figure not shown]
Overview of the time plan for the RELEASE-HF study. EHR, electronic health record; HF, heart failure; NHR, Netherlands Heart Registration; RELEASE-HF, REsponsible roLl-out of E-heAlth through Systematic Evaluation – Heart Failure.

### Data sources

RELEASE-HF will combine various sources of data: the Netherlands Heart Registration (NHR) HF registry, other national databases, interviews, electronic health records (EHR) and telemedicine-generated data (figure 2). A detailed description of each data source is provided in the following:

**Figure 2 F2:**
[figure not shown]
Data sources and flow to set up the final RELEASE-HF data set. H4D, Heart4Data consortium; HF, heart failure; NHR, Netherlands Heart Registration; RELEASE-HF, REsponsible roLl-out of E-heAlth through Systematic Evaluation – Heart Failure.

#### HF registry

The HF registry is an ongoing quality registry in the Netherlands facilitated by the NHR, a non-profit organisation that aims to contribute to quality improvement and safety in cardiac care.^29 30^ The HF registry serves as an ongoing learning healthcare system through benchmarking and quality control. Since 2019, it has been introduced as a voluntary, nationwide HF registration. Patient data are collected non-consecutively, and for the registry no informed consent is asked. Data of included patients are collected at three timepoints: at baseline, 6 months and 12 months from the time since diagnosis. The HF registry includes variables on three levels defined in a data dictionary: patient characteristics, treatment characteristics and clinically relevant outcomes. The data dictionary is a dynamic document (ie, the included variables and definitions may change over time) because it is based on current HF guidelines and compiled by a committee consisting of delegated cardiologists from Dutch hospitals. A detailed up-to-date data dictionary with an overview of the variables collected within the HF registry is always published on the NHR website. Online supplemental material 1 provides an overview of the data dictionary of the HF registry, September 2022 version; the content is subject to change.^31^

10.1136/bmjopen-2023-078021.supp1Supplementary data

#### National registries and databases

If legally and technically feasible, we plan to link the HF registry data, specific to RELEASE-HF, to external data sources to (1) complement missing variables, (2) enrich and validate the HF registry, and (3) reduce registration burden for healthcare professionals/data managers. The external data sources considered are Statistics Netherlands (CBS), the national health insurance database (VEKTIS), the national registry for hospital care (Dutch Hospital Data) and the national database for drug utilisation and drug safety (PHARMO). The variables of interest are visits to the outpatient clinic, to the emergency room and to the general practitioner related to HF, admission days at an intensive care unit, and treatment characteristics specific to HF (ie, medication as class of diuretics).

#### Interviews on the use of telemedicine

Separate data collection will be performed using semistructured interviews among clinicians and finance department staff on the features and costs of telemedicine at the hospital level. Online supplemental material 2 provides the interview guide.

10.1136/bmjopen-2023-078021.supp2Supplementary data

#### EHR and telemedicine-generated data

File search in the EHR of patients and telemedicine-generated data will be used to identify telemedicine components at the patient level.

### Study population

The HF registry comprises patients admitted to a Dutch hospital or to an outpatient clinic for HF irrespective of telemedicine use (figure 1). All patients who meet the diagnostic criteria for HF and its phenotype, according to the European Society of Cardiology (ESC) 2021 guidelines on HF, are included.^1^ If a patient has been diagnosed with HF in a setting other than the one where the patient currently presents (primary, secondary or tertiary care), the patient will also be included.^31^ Current HF registry is not yet incorporated and implemented in care pathways in EHR systems; therefore, selected patients fulfilling the NHR criteria are included in the HF registry and not on a consecutive basis or full coverage of all patients at the outpatient HF clinic. This may lead to selection bias. To prevent this selection bias, a researcher of RELEASE-HF is alerting healthcare professionals regularly to include all patients with HF in the HF registry, regardless of their telemedicine use, treatment and disease severity. Additionally, national working groups are progressing to fully incorporate the HF registry into the EHR.

### Outcome measures

#### Primary outcome

The number of days alive without unplanned hospitalisation within 1 year of follow-up is derived from the number of unplanned hospital days as collected in the HF registry (table 1).

**Table 1 T1:** Operationalisation of exposure variable and study outcomes

Variable	Source	Time of collection	Operationalisation
Exposure			
Telemedicine	HF registry, telemedicine-generated data	T0, T1*, T2	Whether a patient receives telemedicine. Five categories: (1) no telemonitoring†; (2) telemonitoring by telephone; (3) telemonitoring, non-invasive based on traditional parameters (eg, blood pressure, ECG); (4) telemonitoring using ICD based on HF parameters; and (5) telemonitoring, invasive using sensors in the bloodstream or heart.
Primary outcome			
Number of days spent alive without unplanned hospitalisations within 1 year of follow-up	HF registry	T1*, T2	Number of days directly related to unplanned cardiac hospital admission due to HF. Number of admission days will be summed up over a period between follow-up moments and subtracted from 365 days.
Secondary outcomes			
Costs	Derived from HF registry, external data source, EHR, interviews	T0, T1*, T2	Costs estimated from patient, disease and treatment characteristics. Information taken into account includes medication use, whether the patient underwent cardiac interventions (eg, pacemaker implantation, percutaneous coronary intervention), use of telemedicine, hospital admission days, visits to the outpatient clinic, visits to the emergency room, admission days at an intensive care unit and visits to the GP related to HF.
All-cause mortality	HF registry, external data source	T1*, T2	Mortality status, determined after verification at the Personal Records Database (in Dutch: Basisregistratie Personen). Mortality is independent of HF (all-cause).
Functional status	HF registry	T0, T1*, T2	NYHA classification: a functional classification of patients based on severity of symptoms and physical activity, with specific attention to fatigue, palpitation and dyspnoea. Scores are linked to one of four NYHA classes: class I: no limitation; class II: slight limitation; class III: marked limitation; and class IV: unable to carry on any physical activity without discomfort.^1^
Health status	HF registry	T0, T1*, T2	SF-36 or SF-12 questionnaire (subset of SF-36)^54^: a validated patient-reported survey of patient health. Both questionnaires consist of eight sections with scores: vitality, physical functioning, bodily pain, general health perceptions, physical role functioning, emotional role functioning, social role functioning and mental health. Each score is transformed into a scale of 0–100 on the assumption that each question carries equal weight. The lower the score, the more disability.
Health-related quality of life	HF registry	T0, T1*, T2	SF-36 or SF-12 questionnaire. QALY will be calculated based on the SF-6D, a model in which a single, preference-based score can be directly calculated for the SF-36 and SF-12.^55^ Scores range from 0.0 (worst health state) to 1.0 (best health state).
Healthcare utilisation	External data source, EHR	T1, T2	Healthcare utilisation based on (1) the number of outpatient visits, plus (2) the number of visits to the general practice related to HF.

*The HF registry collects data standard at baseline (T0), after 6 months (T1) and after 12 months (T2). The RELEASE-HF study conforms to the timeframes of the HF registry. Therefore, data will be collected at 6 months, although the outcome measurements are after 12 months.

†The HF registry defines telemedicine as telemonitoring.

EHR, electronic health record; GP, general practitioner; HF, heart failure; ICD, implantable cardioverter defibrillator; NYHA, New York Heart Association; QALY, quality-adjusted life year; RELEASE-HF, REsponsible roLl-out of E-heAlth through Systematic Evaluation – Heart Failure; SF-12, 12-item short form health survey; SF-36, 36-item short form health survey; SF-6D, six-dimensional health state short form.

#### Secondary outcomes

The secondary outcomes are all-cause mortality, functional status, health status, health-related quality of life (hrQoL), healthcare utilisation within 1 year of follow-up and costs of care (table 1).

### Exposure measurement

Exposure to telemedicine is measured in the HF registry at 6 months and 12 months of follow-up as non-use of telemedicine, telephone only, non-invasive telemedicine, implantable cardioverter defibrillator-based telemedicine or invasive telemedicine (table 1). Telemedicine output can be different from the closed-ended interviews that correspond to all outpatient clinic contacts in general. The components of the telemedicine intervention will be assessed at the hospital level at one time during the follow-up period. Table 2 provides an overview and operationalisation of the main components of the telemedicine intervention that have been described in existing literature or at the local (eg, hospital) level.^7 32–34^ The components will be validated and possibly further refined based on the interviews. Figure 3 illustrates the flow of data collected at the hospital level and at the patient level.

**Table 2 T2:** Overview and operationalisation of telemedicine variables collected in the qualitative study

Component	Definition	Operationalisation (examples)
Supplier	(External) supplier of telemedicine for patients with HF.	Sanacoach, Luscii, Motiva/Philips, linked in personal environment in EHR.
Purpose of telemedicine	The intention/motives for which the telemedicine intervention is administered: patient level and/or hospital level.	Monitoring, prevent exacerbation, reduce workload, reduce costs, patient-centred care.
Considering telemedicine	First time a clinician considered telemedicine in HF management.	After diagnosis, (re)hospitalisation, titration phase.
Structured telephone support	Structured monitoring by telephone without using applications or devices specific to telemedicine and monitoring HF.	Present or not present.
Applications	Technologies or platforms on which the patient could receive telemedicine.	Smartphone, tablet, laptop, television, smartwatch.
Devices	Accessory a patient could use to perform telemedicine.	Blood pressure device (with or without Bluetooth), weight scale (with or without Bluetooth), smartwatch.
Involved healthcare workers	Involved healthcare workers and their role in considering and executing telemedicine.	HF nurse, nurse specialist, cardiologist.
Control centrum	The presence or absence of a control centrum to check the submitted measurements and questions.	Present or not present.
Use of telemedicine	When a patient could use telemedicine and have contact with clinicians.	24/7, office hours, during weekend, at night.
Type of contact	The manner of contact between the clinician and the patient.	Direct or indirect (store-and-forward) contact with a clinician.
Measurements	Type of measurements: vital functions and HF-related complaints, used to detect deterioration of and/or to monitor HF.	Blood pressure, heart rate, weight, temperature, oxygen level, HF complaints such as swelling ankles, nocturia, shortness of breath, tiredness, loss of appetite, coughing/wheezing, dizziness.
Notifications	Messages from the telemedicine intervention. Notifications can be two-sided: from patient to clinician and vice versa.	Automatic or non-automatic generated messages; notifications present or not present.
Modifiable aspects	The option to set up *thresholds* of monitored vital function, and the possibility to tailor these thresholds per patient, severity, type of HF or other aspects of the telemedicine intervention (eg, set up a tele-education environment).	Available or not available.
Connection with EHR	Feature of telemedicine if the intervention is integrated with the EHR. This means that data entered by the patient through the telemedicine intervention are visible to the clinician in the EHR without using other applications.	Connected or not connected with EHR.
Education	The presence or absence of an educational environment and the manner in which this is shaped.	Present or not present.
Educational topics	The covered topics in the educational environment of telemedicine.	Nutrition, behaviour, exercise, medication.
Self-care	The presence or absence of self-care modules and the actions taken by the patient based on a digital advice or measurement.	Available or not available.
Protocol	Local (hospital) protocol which consists of definitions about how often a patient should use telemedicine/monitor the vital signs and HF complaints, depending on the HF complaints or phase (ie, titration, stable monitoring).	Low-intensity protocol defined as measurement of vital signs <2 times per week. High-intensity protocol defined as measurement of vital signs ≥2 times per week.

EHR, electronic health record; HF, heart failure.

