### Data collection and quality control

Data of the HF registry will be remotely monitored for major outliers and missing variables using the NHR; these processes have been described elsewhere.^30 35^ The NHR uses a unique individual patient identifier (NHRpersonID) to deduplicate registrations of the same patient (at the same or different hospitals) in the HF registry.^36^ During the RELEASE-HF study, researchers will perform an additional check on completed data and provide assistance to hospitals to reduce missing values, as well as assistance to reduce registration burden.

Telemedicine interviews, using an interview guide with closed-ended questions, will be performed by a RELEASE-HF investigator and conducted with clinicians (eg, cardiologist, HF nurse, nurse specialist, physician assistant). Interviews will be held during the 36-month period of data collection. All hospitals with telemedicine in HF care will be interviewed once, and the data will be checked with the hospitals once during the data collection period to be aware of changes in the components and status of telemedicine. For each hospital, the 6-monthly costs of telemedicine are determined via interviews and registration data (if at hand). The units will be linked to the unit cost guideline provided by the Dutch National Health Care Institute (Dutch: Zorginstituut Nederland).^37^ These interviews will be performed by a health technology assessment (HTA) scientist and conducted with clinicians or finance department staff. All participants will provide informed consent.

Patient-level telemedicine data are collected by a clinician, data manager or researcher at the hospital where the patient is being treated because these individuals have access to the identification log of the HF registry. Collected data will include the start date of telemedicine use and the frequency at which measurements are sent to the treating hospital, with a high rate typically referred to as a high-intensity (or acute) protocol and a low rate as a low-intensity (or stable) protocol.

The Heart4Data consortium will establish opportunities for data linkage between the HF registry and other national registry databases, in collaboration with public partners (figure 2).^28^ At the time of writing, a collaboration between these databases and the HF registry is not yet established for all external national databases.

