##### Preparation of the statistical model

As a first step, we describe how the overall effect of offering any type of telemedicine versus not offering telemedicine will be estimated. This analysis will subsequently be used for a comparison of telemedicine effects on days alive without unplanned HF-related hospitalisation during 1 year across subgroups.

The cohort is restricted to individuals with newly diagnosed HF, that is, at most 3 months prior to baseline. The exposure contrast is defined as offering any type of telemedicine after first presentation with HF at the hospital outpatient clinic versus patients not offered telemedicine. The telemedicine status for the entire follow-up is defined by 6 months after baseline measurement of telemedicine, used as an observational analogue of an ‘intention to treat’ analysis in which the stopping of telemedicine is disregarded.

Because telemedicine administration is dependent on patient characteristics, confounding by indication will be accounted for. Based on clinical consensus, the following patient-level confounding variables measured at baseline will be adjusted for: age, sex, SES, BMI, NYHA, LVEF, aetiology of HF, systolic blood pressure, diastolic blood pressure, heart rhythm, heart rate, chronic respiratory disorders, OSAS, stroke, extra cardiac arterial vascular pathology, DM, hypertension, anaemia, CKD, malignancy, heart rhythm disorders, depression and thyroid disease (see table 3 and online supplemental material 1).

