#### Cost-effectiveness

Costs will be estimated by computing the average costs (using cost guideline provided by the National Health Care Institute) per individual based on the information collected by the NHR and in the interviews with hospitals. Since 2023, Dutch hospitals can claim costs of telemedicine using the National Health Care Institute’s Diagnosis Treatment Combination (DBC). This DBC can be used to estimate the average costs.^37^ A 95% credible interval (CE) will be computed using the percentiles of a Monte Carlo bootstrap analysis with 5000 resamplings. This average cost represents a sum of the costs of telemedicine use, inpatient days, days at intensive care unit, HF-related hospital procedures and outpatient visits. In a secondary analysis, we will re-estimate the average costs and 95% CE using data enriched with VEKTIS data (if linking is available), meaning that the costs of visits to the general practitioner, pharmacy and care at home are also taken into account.

Linkage with CBS may be incomplete for several participants because of missing values or incomplete data sets (eg, twins, different available time windows between registries of collected data). If the number of non-linked participants is below 10%, we will perform multiple imputation; if it is above 10%, we will perform HTA analysis on the complete subset.

Utility values will be estimated using the average hrQoL score collected in the HF registry and, if needed, from the literature. The difference in average QoL score between the group that uses telemedicine versus the group that does not represents the difference in disutility between the groups under the assumption that the collected hrQoL is a good representation of the utility of the particular health state that individuals were in.

Quality-adjusted life years (QALYs) are estimated by multiplying the observed number of follow-up years by the corresponding hrQoL score. Subsequently, the incremental cost-effectiveness ratio (ICER) is computed by taking the ratio between the difference of the costs of the average patient in the telemedicine group and those not in the telemedicine group, and the difference in QALY of both groups, thereby providing the cost per additional QALY gained. The 95% CEs are obtained using the Monte Carlo percentile methods described above. Both deterministic and probabilistic sensitivity analyses will be performed to completely outline uncertainty on individual and combined parameters in the model.

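### Telemedicine is expected to change during the study, but no stated model adjusts for calendar time and hospital component status carries no dates, so secular change can enter the effect estimates and some RQ2/RQ4 patients can be mislabelled

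*Protocol article*

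**What the plan says.** **Change over time is part of the design.** Under Study design, the investigators will "simultaneously observe the natural (de)implementation of telemedicine". The study began in June 2021 and runs for 4 years, and hospitals may join later (Progress and time plan). Under Cost-effectiveness: "Since 2023, Dutch hospitals can claim costs of telemedicine". The registry's dictionary is dynamic, in that "the included variables and definitions may change over time" (HF registry). Inclusion is not consecutive, and efforts to widen it are under way (Study population).

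**Component exposure.** Under Exposure measurement: "The components of the telemedicine intervention will be assessed at the hospital level at one time during the follow-up period". Data collection and quality control says "Interviews will be held during the 36-month period of data collection" and "All hospitals with telemedicine in HF care will be interviewed once", and adds that "the data will be checked with the hospitals once during the data collection period to be aware of changes in the components and status". The Research question 2 section then sets presence or absence of a component at hospital level. RQ4 reuses component contrasts, which I read as those of RQ2.

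**Adjustment.** Preparation of the statistical model says that "the following patient-level confounding variables measured at baseline will be adjusted for" and gives a closed list of demographic and clinical variables. RQ2 adds hospital characteristics. The primary model is a linear mixed model with a random intercept for centre. Neither list contains an inclusion date or period, and the model as specified has no such term.

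**Any-versus-none exposure.** This is each patient's own registry status at 6 months, not a hospital label.

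**The concern.** There are two separate problems.

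*Calendar time.* If uptake rises (or falls) during the study, users and non-users differ in when they entered. Anything else that moves over the same period, such as outcomes, registry coverage or registry definitions, then becomes mixed with the telemedicine effect. The random intercept absorbs stable differences between centres. It does not absorb a trend within a centre. The primary effect and the RQ1 stratum effects are exposed to this. RQ2 is exposed too if component prevalence shifts over time.

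*Component labels.* A hospital that adds or drops a service centre, an educational module or a high-intensity protocol during the study has telemedicine patients on both sides of the change. With one undated label, some of them are analysed under a component status they did not have. This touches RQ2 and RQ4 only.

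**Working it through.** **The yardstick.** Sample size calculation gives 6.4 days, SD 21.1, 5% error (two-sided assumed), 80% power, 20% dropout; 1:1 allocation is assumed. Per arm, n = 2 × (1.96 + 0.84)² × 21.1² / 6.4² gives 171, so 342 in total, and 342/0.8 gives 428. A t-based calculation gives 172 per arm and 430. The stated 432 is within 1% of both. 432 × 12 = 5184 and 5184/0.8 = 6480 are exact. The point does not turn on these figures; the 6.4 days serves only as a scale.

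**Calendar time.** The document gives neither an outcome trend nor an uptake curve, so every input here is assumed. Let s be the outcome trend in days per year and g the difference in mean entry date between users and non-users. The bias from omitting calendar time is s × g. With entry uniform over T years and uptake linear from p0 to p1, with mean p̄:

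g = [(p1 − p0) × T / 12] / [p̄ × (1 − p̄)]

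| Uptake | g, T = 3 | g, T = 2 | Bias (T = 3) at s = 0.5 / 1 / 2 |
|---|---|---|---|
| 30% flat | 0 | 0 | 0 / 0 / 0 days |
| 20% to 40% | 0.05/0.21 = 0.24 y | 0.16 y | 0.12 / 0.24 / 0.48 days |
| 10% to 50% | 0.10/0.21 = 0.48 y | 0.32 y | 0.24 / 0.48 / 0.95 days |
| 10% to 70% | 0.15/0.24 = 0.63 y | 0.42 y | 0.31 / 0.63 / 1.25 days |

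Across the rising-uptake rows the bias is 0.12 to 1.25 days, that is 0.12/6.4 = 2% to 1.25/6.4 = 20% of the assumed effect. T = 2 is shown because 36 months is the length of data collection and each patient needs 12 months of follow-up; if follow-up lies inside that window, entry spans about 24 months. The gaps are then one third smaller, and the bias runs from 0.5 × 0.16 = 0.08 to 2 × 0.42 = 0.83 days (1% to 13%). The sign follows the signs of the trend and of the change in uptake.

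**Interactions.** The bias in a difference between subgroups A and B is s_A × g_A − s_B × g_B. It is zero when trend and date gap are the same in both. As an illustration, with s = 1 in both and gaps of 0.625 and 0.238 years, it is 0.39 days, or 12% of a 3.2-day and 10% of a 3.8-day interaction.

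**Component labels.** Suppose a hospital changes a component once at a random time, its status is read once at a random time, and its telemedicine patients enter evenly. The share mislabelled is the expected distance between two uniform times, 1/3. With 10%, 25% or 50% of hospitals changing (assumed), the overall share is 0.10/3 = 3%, 0.25/3 = 8% or 0.50/3 = 17%.

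If the re-check were used and a detected change dated at the midpoint of the two contacts, the 1/3 falls to 5/24 = 0.21. The change falls between the contacts one third of the time, with mean error 1/8; otherwise it falls outside them, with mean error 1/4; and 1/3 × 1/8 + 2/3 × 1/4 = 5/24. The overall range becomes 2% to 10%. So the re-check helps if it is used, but most changes (two in three) fall outside the two contacts unless dates are asked for.

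If a share m of each labelled group is wrong, and the wrongly labelled patients are otherwise comparable, the contrast is multiplied by (1 − 2m): 0.8 at m = 10% and 0.6 at m = 20%. That comparability is an assumption. If outcomes also drift over time, patients from before a change differ in outcome as well, and the direction of the bias is no longer fixed.

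**The case against.** The strongest reply is that the article condenses a fuller plan, that its first list is explicitly of patient-level confounders, and that a period term and dating rules may stand elsewhere. That is possible. But the article does state the covariate set, the additions for RQ2 and the model, and calendar time is in none of them.

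A second reply is that the components are not a bare snapshot. There is a re-check, telemedicine start date and measurement frequency are collected per patient, a file search of records is meant to identify components for individual patients, and hospital-level measurement is declared as a limitation. This stands in part. However, a patient's start date and measurement frequency do not date a service centre or an educational module, and the RQ2 section still fixes the contrast at hospital level. No section says what happens to a change once it is found.

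Several stronger readings are tempting and are not supported:

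- *Accrual lasts 36 months.* The text gives 36 months of data collection.
- *Users enrol a year later than non-users.* With linear uptake over 36 months that needs a rise from 0% to 100% (0.25/0.25 = 1 year), and the Discussion says telemedicine is already in use.
- *The whole secular bias falls on the 3.2 to 3.8 day interactions.* A bias shared by subgroups cancels.
- *Component error always pulls towards no difference.* That holds only if mislabelled patients are otherwise comparable.
- *Telemedicine users and non-users are mislabelled by the hospital snapshot.* Their status is recorded per patient.
- *The 2023 reimbursement and the changing dictionary prove a trend.* They make one plausible; the document reports no change in uptake or in the outcome definition.

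**Conclusion.** The point holds as a risk that the stated plan leaves open, not as a demonstrated bias. The protocol expects exposure to change over time and lists no calendar-time adjustment. Under the assumed scenarios this could shift the any-telemedicine contrast by about 0.1 to 1.25 days (2% to 20% of 6.4 days), about one third less if entry spans 24 months, and not at all if either uptake or outcome is flat. The sign can go either way. Interactions are affected only where the trend or the user/non-user date gap differs between subgroups.

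For RQ2 and RQ4, an undated hospital label could misplace about 3% to 17% of patients if 10% to 50% of hospitals change a component once; the direction is not fixed. The sections Exposure measurement and Data collection and quality control need reconciling on how a detected change is used. The change is worth making because it is cheap and because dates recalled late are unreliable.

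**What to change.** 1. Add the calendar date of T0, as a spline or in half-year periods, to the covariates of the primary, RQ1 and RQ2 models. The registry should already hold this date, since the cohort is restricted by time from diagnosis to baseline and the outcome is rescaled to days under follow-up.
2. In the planned interview and re-check, record the start and stop date of each RQ2 component. Give each telemedicine patient the status in force at his or her telemedicine start date, or at T0 where that date is missing. The start date is the better anchor because telemedicine can begin after T0 and is read at 6 months. Reword Exposure measurement and Data collection and quality control to agree with this.
3. Add a sensitivity analysis that excludes patients whose follow-up spans a change in the component being contrasted.

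Cost: a few date fields in contacts already planned and one more covariate. Expect a slight loss of precision, mainly where uptake is closely tied to calendar time, and some recall error in the component dates.
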